## Abstract

**Background:**

It has often been hypothesized that the frequency of follow-up visits for patients with early-stage endometrial cancer could be decreased. However, studies evaluating effects of a reduced follow-up schedule among this patient group are lacking. The aim of this study is to assess patient satisfaction and cost-effectiveness of a less frequent follow-up schedule compared to the schedule according to the Dutch guideline.

**Methods:**

In this multicenter randomized controlled trial, patients diagnosed in the Netherlands with stage 1A and 1B low-risk endometrial cancer, for whom adjuvant radiotherapy is not indicated (*n* = 282), are randomized. Patients allocated to the intervention group receive four follow-up visits during three years. Patients allocated to the control group receive 10–13 follow-up visits during five years, according to the Dutch guideline. Patients are asked to fill out a questionnaire at baseline and after 6, 12, 36, and 60 months. Primary outcomes include patient satisfaction with follow-up care and cost-effectiveness. Secondary outcomes include healthcare use, adherence to schedule, health-related quality of life, fear of recurrence, anxiety and depression, information provision, recurrence, and survival. Linear regression analyses will be used to assess differences in patient satisfaction with follow-up care between intervention and control group.

**Discussion:**

We anticipate that patients in the intervention arm have a similar satisfaction with follow-up care and overall outcomes, but lower healthcare use and costs than patients in the control arm. No differences are expected in quality-adjusted life-years and satisfaction, but the reduced schedule is expected to be cost-saving when implemented in the Netherlands.

**Trial registration:**

ClinicalTrials.gov, NCT02413606. Registered on 10 April 2015.

**Electronic supplementary material:**

The online version of this article (10.1186/s13063-018-2611-x) contains supplementary material, which is available to authorized users.

## Background

Endometrial cancer is the most common gynecological cancer, with about 1900 newly diagnosed patients per year in the Netherlands. Today, about 20,000 women living in the Netherlands have survived endometrial cancer, of whom almost 8000 were diagnosed in the past five years and are currently receiving follow-up care [1]. Women with early-stage cancer (55%) with favorable features receive surgery only, while those with risk factors or with more advanced stages generally receive adjuvant radiotherapy [2]. Most patients are followed after treatment for five years according to the current guideline, with hospital visits every three or four months in the first two years after treatment, every 4–6 months in the third year, and annually in the fourth and fifth years. Reasons for follow-up include early diagnosis of recurrences—for which curative treatment is available, signaling and treating adverse events of cancer and treatment, psychosocial support, and information provision [3, 4].

The optimal follow-up schedule for patients with endometrial cancer is unknown [4–8]. As a result, guidelines in the Netherlands are consensus-based and do not take risk profile into account. Due to current emphasis on providing high-quality care at lower costs, a critical evaluation of current follow-up practices for cancer patients is needed [9–11]. The transition of follow-up care to the nurse specialist [12, 13] or primary care physician [14, 15] has been presented as a means to increase the cost-effectiveness of follow-up care. However, reduction of the frequency and duration of follow-up visits has not yet been evaluated [4, 10].

Current evidence provides a multitude of reasons that support reduction of standard follow-up visits. First, there is no survival benefit in the detection of asymptomatic recurrences at routine follow-up, compared with symptomatic recurrence or interval detection [4, 5, 8, 16–18], probably because the recurrence rate of early-stage endometrial cancer survivors is low (3%) and because most recurrences (70%) present with symptoms [5]. The majority (70–100%) of the recurrences occur within three years [5]. Second, side-effects from treatments are found in only 6% of the stage 1 patients who received surgery (hysterectomy and salpingo-oophorectomy) alone [2, 19]. Third, follow-up visits evoke distress around the time of the visits [15, 17, 20–22]. Finally, alternative follow-up schedules in other cancer populations do not show decreased patient satisfaction or health-related quality of life (HRQoL) [23, 24]. At the same time, there are reasons to retain some follow-up care, including that follow-up is beneficial for patients for reassurance [15, 21, 25], to provide support for psychosocial, physical, and sexual problems [2, 3, 24], and to provide information [26] and tertiary prevention care [27].

These findings suggest that most early-stage endometrial cancer patients do not need intensive follow-up to detect recurrences, improve survival, or discuss consequences of treatment. However, patients may need *some* follow-up to detect information needs and provide psychosocial counseling. Therefore, a reduced follow-up schedule for low-risk, early-stage endometrial cancer patients should focus on eliminating unnecessary care, which is expected to result in decreased patient worry around visits, prevent wrong patient expectations, and save healthcare costs. At the same time, a minimal number of follow-up visits is needed to support necessary patient counseling and information provision [8–10].

Additionally, it is increasingly recognized that cancer survivors should be provided with information about their disease, treatment, care providers, physical and psychosocial consequences of their cancer and its treatment, care services, and health promotion information [28, 29]. The Institute of Medicine recommends the use of Survivorship Care Plans to provide cancer survivors this information [28]. Although Survivorship Care Plans did not increase satisfaction with information provision and care among gynecological cancer patients [30, 31], they may support symptom monitoring. Adequate monitoring of symptoms by patients would enhance early detection of symptomatic recurrences while limiting the need for follow-up visits.

To obtain evidence on the effects of a reduced follow-up schedule we propose to conduct a nationwide randomized controlled trial (RCT) to study the effects of a reduced follow-up schedule for patients with endometrial cancer. We hypothesized that the patients in the intervention group report at least similar levels of patients’ satisfaction with care at lower costs.

## Methods/Design

### Objectives and hypotheses

The aim of this study is to compare a reduced follow-up schedule of four visits in three years among low-risk, early-stage endometrial cancer survivors, with the schedule according to the current Dutch guideline that includes 10–13 visits in five years. Primary outcomes include patient satisfaction with follow-up care and costs-effectiveness from the healthcare perspective. Secondary outcomes include healthcare use, adherence to the indicated follow-up protocols, reasons for non-adherence, HRQoL, worry including fear of recurrence, anxiety and depression, satisfaction with information provision, healthcare providers’ satisfaction with follow-up schedule, time till recurrence, and survival.

We hypothesize that endometrial cancer patients in the intervention arm of the study are not less satisfied with the follow-up care and do not report worse HRQoL, fear of recurrence, anxiety, depression, and information provision satisfaction. We furthermore hypothesize that healthcare use and associated costs will be lower in the intervention arm, resulting in a cost-effective intervention. More precisely, we expect that by reducing the follow-up schedule from 10–13 to four visits, the costs of these visits will be saved, although some substitution might occur to care by the specialist, specialized nurse, or general practitioner. From a healthcare perspective, we expect this alternative follow-up schedule will save costs.

### Design

A national multicenter (non-inferiority) RCT among 282 endometrial cancer survivors will be conducted. Patients will be randomized 1:1 in the intervention or control group. Since differences in outcomes between groups are expected to be most pronounced within the first three years of follow-up and the largest cost-saving is achieved within three years, we will evaluate this study in a two-step approach, with an evaluation after one, three, and five years. After five years, the follow-up according to the guideline ends. Patients in both arms receive a Survivorship Care Plan, with information on symptoms which would necessitate a consultation.

Doctors and patients cannot be blinded for intervention or control group assignment. A questionnaire will be sent to all patients at baseline (after primary treatment), and 6, 12, 36, and 60 months later. The baseline questionnaire will be assessed before the intervention under study, that is the different follow-up schedules, starts. Healthcare use, recurrences, survival, and costs will be assessed after three and five years. A schedule of the study is presented in Fig. 1. Healthcare professionals will receive a questionnaire at the end of the study. In addition, a non-participation study will be performed registering hospital healthcare use and assessing patient-reported outcomes using a questionnaire. Medical Ethics approval will be obtained before the start of this project.

**Fig. 1 Fig1:**
[figure not shown]
SPIRIT checklist: schedule of enrolment, interventions, and assessments

### Setting

Hospitals throughout the Netherlands can participate. In total, 46 centers (both academic and non-academic centers) will include patients. Participating centers are listed at http://www.ClinicalTrials.gov. Inclusion will take approximately 2.5 years.

### Study population

Low-risk, early-stage endometrial cancer survivors who receive no adjuvant (radio)therapy after initial surgery will be included in the study.

### Inclusion criteria

Patients with endometrioid type endometrial carcinoma with stage 1 (FIGO, 2009) low-risk disease, with the following combination of stage, age, and grade will be eligible: (1) stage 1A, any age, grade 1 or 2; or (2) stage 1B, < 60 years, grade 1 or 2 without lymphovascular space invasion (LVSI). Other inclusion criteria are written informed consent and sufficient oral and written command of the Dutch language. Tumor stage, grade, and type should be histological confirmed by the pathologist before inclusion.

### Exclusion criteria

Exclusion criteria include: (1) any other stage and type of endometrial carcinoma; (2) histological types papillary serous carcinoma or clear cell carcinoma; (3) uterine sarcoma (including carcinosarcoma); (4) receive radiotherapy for current endometrial carcinoma; (5) previous malignancy (except for non-melanomatous skin cancer) < 5 years; (6) having metastases of other tumors; (7) confirmed Lynch syndrome; and (8) previous pelvic radiotherapy**.**

### Recruitment

The national Trial Office of the Netherlands Comprehensive Cancer Organization (IKNL) will organize data collection. Patient-reported outcomes will be obtained by questionnaires [32]. Informed consent will be asked by the treating gynecologist during the postoperative visit. The patient is provided information about the study and an informed consent form. Patients have 2–4 weeks to consider the proposal and can ask questions for instance during an extra visit or a telephone call. In the visit 5–7 weeks after diagnosis, the patient signs the written informed consent and provides address information, in case she is willing to participate. The gynecologist fills out the Randomization Form and sends it to the IKNL Trial Office, who performs the randomization. The patient receives the paper questionnaire and a pre-stamped envelope, to be completed at home. The patients send the completed questionnaire to the IKNL Trial Office. At 6, 12, 36, and 36 months the participant will receive a questionnaire plus pre-stamped envelope at their home address. Non-respondents will be sent a reminder letter and questionnaire within six weeks. Only for the baseline questionnaire will this procedure will be faster to assure a proper baseline measure (reminder through the local principal investigator or research nurse after two weeks). If the patient moves to another hospital, a form will be used to obtain patient data from the new hospital. If the patient does not want to participate in the trial, she is still asked to fill out a single questionnaire and consent to assess healthcare use information, allowing the researchers to compare participants and non-participants. If the patient agrees, the gynecologist completes the registration form for non-participants and sends it to the IKNL Trial Office. The gynecologist provides the patients with a set including a short one-time questionnaire, an informed consent form to assess healthcare use data and a pre-stamped envelope. No other data will be collected for this patient. Questionnaires will be scanned and the database will be checked for a sample of ten patients. On the total database, range and consistency checks will be conducted. Clinical research forms (CRF) will be completed directly in a program.

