### Randomization

Patients are randomized via a randomization program, using a computer-generated list of random numbers. Block randomization will be used (no stratification) to assure approximately equal numbers in both groups. Concealment of randomization allocation is guaranteed by the fact that only after written informed consent, the trial manager obtains the randomization allocation from the randomization program and sends it to the gynecologist.

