### Statistical analysis

Data will be analyzed after one, three, and five years of follow-up. All patients will be included in the analyses and all patients will be analyzed according to the arm to which they were assigned (intention-to-treat). In addition, per protocol analyses will be conducted including patients who received follow-up care as intended in the trial arms. Intention-to-treat and per-protocol analyses are both important in non-inferiority trials. Data will be analyzed using descriptive statistics, linear, and logistic regression analyses. Primary outcome is satisfaction with follow-up care over three-year follow-up. The primary outcome will be analyzed one-sided. Secondary outcomes will also be analyzed as non-inferiority using 0.5 SD as a non-inferiority margin, but will be tested two-sided.

Multilevel multivariate linear and logistic regression analyses will be conducted for continuous and dichotomous outcomes, respectively. Analyses will include relevant pre-defined covariates to improve the power. Differential effects by fear of recurrence will be evaluated by adding the interaction term (group*moderator) to the model. We will carry out repeated measures analyses using multilevel linear mixed models, which accounts for the intra-patient dependency of the repeated measures. Missing outcomes will be assumed missing at random (MAR). An advantage of multilevel linear mixed models is that all patients can be included in the analyses, regardless of whether they have been missing some follow-up measurements. All tests will be considered significant if *p* < 0.05. Clinically meaningful differences will be determined with Norman’s “rule of thumb,” whereby a difference of > 0.5 SD indicates a threshold of discriminant change in health status scores of a chronic illness [43]. If we have the baseline data of a patient, we will include this patient in the analysis.

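### Nothing in the plan ensures that the baseline questionnaire is completed before the patient knows her arm, so baseline satisfaction and fear of recurrence may already reflect the allocation

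*Protocol article*

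**What the plan says.** All references are to the protocol article.

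- **Recruitment.** After the patient signs consent, "The gynecologist fills out the Randomization Form and sends it to the IKNL Trial Office, who performs the randomization". The next sentence reads: "The patient receives the paper questionnaire and a pre-stamped envelope, to be completed at home". For late baseline forms there is a faster procedure than for later rounds: "reminder through the local principal investigator or research nurse after two weeks".
- **Randomization.** Once written consent exists, "the trial manager obtains the randomization allocation from the randomization program and sends it to the gynecologist". No returned baseline form is required first.
- **Intervention.** The Survivorship Care Plan is emailed to the patient's caregivers at randomisation. The first visit in the reduced schedule is at 3 months.
- **Design.** "Doctors and patients cannot be blinded for intervention or control group assignment". On timing: "The baseline questionnaire will be assessed before the intervention under study, that is the different follow-up schedules, starts".
- **Statistical analysis.** Pre-defined covariates, not named, will be included. The analysis uses mixed models for repeated measures. "Differential effects by fear of recurrence will be evaluated by adding the interaction term (group*moderator) to the model". All patients are to be analysed as assigned, and the section closes by saying that a patient whose baseline data are available will be included.

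**The concern.** A baseline score can be used freely in the analysis because allocation cannot have affected it. That holds if the score is obtained before randomisation, or at least before the patient knows the result. The plan protects against a different event, the start of the visit schedule. Between disclosure of the arm and the first visit there is a period in which a form would satisfy the Design section and still be completed by a woman who knows whether she will have four visits or 10–13.

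The article gives reasons to think that this knowledge could matter. The Background says that visits reassure patients and also cause distress around the time of the visit. The patient-reported outcomes were chosen because they were expected to respond to follow-up visits.

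Three things are at stake: the adjusted estimate of the primary non-inferiority comparison, the interpretation of the fear-of-recurrence interaction, and the make-up of the analysis set if return of the baseline form influences inclusion.

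**Working it through.** **1. Order of steps.**

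| Step | What it waits for, as written |
|---|---|
| Randomisation by the Trial Office | Signed consent and the Randomization Form |
| Allocation sent to the gynecologist | Written consent |
| Survivorship Care Plan emailed to caregivers | Randomisation |
| Baseline form completed at home | Nothing stated except that the schedules have not started; reminder after two weeks |

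No row makes an allocation step wait for the baseline form, and no row makes the form wait for, or precede, disclosure. Completion after disclosure is therefore possible under the plan.

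**2. The plan's own figures.** The timing point rests on no stated figure. The sample size is reproduced only to fix inputs for the illustration. Inputs from Sample size: margin 6, SD 14.3, power 0.80.

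- n per arm = 2 × (1.960 + 0.842)² × 14.3² / 6² = 89.2, rounded up to 90, so 180 in total. This matches the plan at one-sided 0.025.
- At one-sided 0.05 the same formula gives 71 per arm.
- 180 / (1 − 0.36) = 281.25, rounded up to 282, which matches.

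Because the plan calls the primary test one-sided with alpha 0.05, both levels are shown below.

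**3. Bias if the baseline score is adjusted for.** Let d be the drop in intervention-arm baseline satisfaction caused by knowing the arm, and b the slope of follow-up on baseline score. The adjusted difference is (follow-up difference) − b × (baseline difference). With a baseline difference of −d, the estimate moves by +b × d, towards non-inferiority. Neither d nor b is in the article; both are assumptions.

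- d = 1, b = 0.5: 0.5 points; 0.5 / 6 = 8% of the margin.
- d = 3, b = 0.5: 1.5 points; 1.5 / 6 = 25% of the margin.
- Wider range, d = 1 to 4 and b = 0.3 to 0.7: 0.3 to 2.8 points, or 5 to 47% of the margin.

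**4. Effect on error rates.** Assume 90 per arm, a true deficit equal to the margin, equal SDs at both times (so b is also the correlation), and no clustering. The standard error is 14.3 × √(1 − 0.5²) × √(2/90) = 1.85. The false non-inferiority rate is Φ(bias / SE − z).

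| d (b = 0.5) | Bias | Nominal 0.025 becomes | Nominal 0.05 becomes |
|---|---|---|---|
| 1 | 0.5 | 0.046 | 0.085 |
| 3 | 1.5 | 0.126 | 0.203 |

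**5. Opposite direction.** If knowing the arm raises intervention-arm baseline scores by 3 points, the bias is −1.5. With no true difference, power at one-sided 0.025 is Φ((6 − 1.5) / 1.85 − 1.96) = 0.68, against 0.90 without the shift.

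**6. Where no bias arises by this route.** A comparison of follow-up scores that uses no baseline score is untouched by steps 3 to 5. The question of who enters the analysis remains.

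**The case against.** The strongest reply is that the article does not state the order. A reader might infer from the sequence of sentences that the baseline form is always filled in after randomisation. The text does not support that. The form may be handed over at the consent visit: later questionnaires are described as arriving at the home address, whereas the baseline reminder runs through the local investigator or research nurse. A patient could complete it that same day, before the Trial Office acts. Nor does the article say when the patient herself is told her arm. The schedule figure and additional files, not available here, may settle both points. All of this stands. It limits the point to what the plan permits, but it does not remove it, because the described procedure contains no hold on the allocation.

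A reader might also infer that the baseline scores are invalid as covariate or moderator. That would follow only if patients knew their arm when answering and this changed their answers; neither is established. The article does not name baseline satisfaction as a covariate, does not give the time point of the moderator, and defines the primary outcome over three years of follow-up rather than as change from baseline.

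Finally, a reader might infer a bias that favours the reduced schedule. The direction is open: since visits can cause distress, news of fewer visits may equally reassure. A shift is also less plausible for the technical and interpersonal parts of the satisfaction scale than for access to care.

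The sponsor did attend to baseline timing, through the faster reminder and the Design sentence. These limit lateness; neither places the form before disclosure.

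**Conclusion.** The point holds as a weakness in the described procedure, not as a demonstrated bias. Randomisation and release of the allocation depend on consent and its paperwork, the baseline form is completed at home with a reminder only after two weeks, and the one safeguard concerns the start of the schedules. In an unblinded trial, some baseline scores may be given with knowledge of the arm.

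The consequence is conditional on the scores being used as covariate, mixed-model baseline or moderator. The bias can then go either way. Its size cannot be found in the article; the illustrative 0.5 to 1.5 points depends on the assumed shift of 1 to 3 points and slope of 0.5. An interaction with fear of recurrence would be hard to interpret if that fear was recorded after disclosure.

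Separately, the closing sentence on inclusion may be meant only to say that baseline data suffice, and the same section promises that all patients are analysed. If it works in practice as a requirement, return of a form after randomisation could select patients differently by arm.

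This is worth correcting because the correction is cheap. It does not by itself undermine the trial.

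**What to change.** - **Future patients.** Have the baseline questionnaire completed at the consent-signing visit, or beforehand and handed in once consent is signed. The Trial Office releases the allocation and the Survivorship Care Plan only when the completed form is in hand. State this order in the Recruitment and Randomization sections, and replace the Design safeguard with completion before disclosure of the allocation.
- **Patients already enrolled** (inclusion was open at submission). Record the date of form completion and the date the patient was told her arm. Keep every randomised patient in the intention-to-treat set whether or not a baseline form came back.
- **Analysis.** Add a sensitivity analysis that does not use baseline values completed after disclosure, for the primary comparison and for the fear-of-recurrence interaction. Set the late value aside, not the patient.

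The cost is a delay of days before the allocation is released, against a first reduced-schedule visit at 3 months, plus two dates to record. The sample size stays at 282.
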